## Abstract

**Background:**

There is currently much interest in encouraging individuals to increase physical activity in order to reduce CVD risk. This study has been designed to determine if personalised CVD risk appreciation can increase physical activity in adults at high risk of CVD.

**Methods/Design:**

In a 2 × 2 factorial design participants are allocated at random to a personalised 10-year CVD risk estimate or numerical CVD risk factor values (systolic blood pressure, LDL cholesterol and fasting glucose) and, simultaneously, to receive a brief lifestyle advice intervention targeting physical activity, diet and smoking cessation or not. We aim to recruit 200 participants from Oxfordshire primary care practices. Eligibility criteria include adults age 40–70 years, estimated 10-year CVD risk ≥20%, ability to read and write English, no known CVD and no physical disability or other condition reducing the ability to walk. Primary outcome is physical activity measured by ActiGraph accelerometer with biochemical, anthropometrical and psychological measures as additional outcomes. Primary analysis is between group physical activity differences at one month powered to detect a difference of 30,000 total counts per day of physical activity between the groups. Additional analyses will seek to further elucidate the relationship between the provision of risk information, and intention to change behaviour and to determine the impact of both interventions on clinical and anthropometrical measures including fasting and 2 hour plasma glucose, fructosamine, serum cotinine, plasma vitamin C, body fat percentage and blood pressure.

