**Figure 1 F1:**
[figure not shown]

Physical activity, clinical and psychological information will be collected before randomisation and one month after delivery of the intervention. A personalised CVD risk estimate and lifestyle advice will be provided to all participants at the end of 4 weeks making it a waiting-list control design. The inclusion of a control group receiving neither a risk estimate or lifestyle advice but undergoing baseline and follow up measurement will control for Hawthorne effects[19].

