### Sample size and rate of recruitment

The study has 80% power at the 5% level of significance to detect a difference of 30,000 total accelerometer counts per day of physical activity between the groups with a sample size of 46 per cell, assuming the estimated total counts per day is mean (SD) 275,400 (101,600) minutes[31]. This equates to 92 participants per arm of the study. We will randomise a total of 200 subjects to allow for a small drop-out rate. We expect retention of study participants to be high because of the short duration and non-invasiveness of the study. Recruitment is anticipated to continue for one year.

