### Statistical analysis

Only data for participants who record at least 500 min/day of activity for at least 4 days during each 7 day period will be analysed. Data will be presented in terms of total body movement (counts·day^-1^), which is an indicator of the total volume of physical activity, and time (minutes·day^-1^) spent at different activity intensity categories averaged per day over the measurement period. Intensity thresholds for sedentary, light, moderate, vigorous and very vigorous intensity physical activity will be defined according to Freedson *et al *and Ekelund *et al*[32,33]. We will also determine the average number of 5- and 10-min bouts of sustained physical activity at moderate or greater intensity allowing 1 min to drop below the threshold for moderate activity in each 5-min bout. We will calculate the proportion of participants in each group accumulating 30 min or more per day of moderate or greater intensity physical activity, the current UK recommendation for physical activity[28]. Data reduction, cleaning, and analyses of accelerometer data will be performed using appropriate software (MAHUffe; see ). Generalized linear model (Poisson distribution or Negative Binomial distribution) as appropriate will be used and estimates of Rate Ratios along with 95% confidence interval will be presented.

Demographic, clinical and biochemical study variables will be summarized using number (percentage) and measures of location and dispersion as appropriate. The change in the study parameters from baseline to one month will be analysed and inference drawn using appropriate statistical methods, keeping in mind the nature of distributions of the study variables. Analysis will be by intention to treat (ITT).

To analyse the highly skewed EQ-5D scores, appropriate non-parametric technique will be used. Other questionnaire data will be analysed using appropriate non-parametric tests to compare average scores as well as distribution of scores in each group. Should a questionnaire generate only a finite number of scores, the data will then be considered polytomous and suitable statistical techniques will be used to analyse any such data.

Any missing biochemical data will be imputed using the Last Observation Carried Forward technique. Any missing accelerometer data however, will not be imputed for.

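### The primary activity model has no stated baseline term, although a valid pre-randomisation accelerometer week is required of every analysed participant

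*Protocol article*

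**What the plan says.** **Primary contrast.** The abstract states: "Primary analysis is between group physical activity differences at one month". The Primary objective section likewise speaks of physical activity at one month.

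**Baseline data.** The text under Figure 1 says: "Physical activity, clinical and psychological information will be collected before randomisation and one month after delivery of the intervention". The Telephone contact section explains that the accelerometer is mailed about a week before visit 1 and worn for seven days. The Statistical analysis section restricts analysis to participants with at least 500 minutes on at least four days in each seven-day period. An analysed participant therefore has a valid baseline week as well as a valid follow-up week.

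**Model.** For accelerometer data, Statistical analysis names a Poisson or negative binomial GLM and reports rate ratios with 95% confidence intervals. It lists no model terms. For the demographic, clinical and biochemical variables it says: "The change in the study parameters from baseline to one month will be analysed". The methods are to be appropriate to each distribution, and no baseline covariate is named.

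**Sample size.** "The study has 80% power at the 5% level of significance to detect a difference of 30,000 total accelerometer counts per day of physical activity", "assuming the estimated total counts per day is mean (SD) 275,400 (101,600) minutes". "This equates to 92 participants per arm of the study". No correlation between baseline and follow-up is given.

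**The concern.** The trial already pays for the baseline week: participants wear the device, and those without a valid week are left out of the analysis. Week-to-week activity within a person is likely to be correlated, and a baseline covariate removes the part of the follow-up variance that this correlation explains. Nothing in the article says that the primary comparison will use it. The sample size rests on the SD of a single measurement, which fits a comparison of follow-up values that ignores baseline.

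For the other outcomes, change from baseline with no baseline covariate would be less precise than a baseline-adjusted analysis at any correlation below 1. It would be less precise than ignoring baseline altogether when the correlation is below 0.5.

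Precision matters here because, on the article's own inputs, an unadjusted comparison falls well short of the stated 80% power. The Randomisation section describes blocks of four without minimisation and names no stratification factor, so nothing stated in the design balances baseline activity.

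**Working it through.** **Inputs from Sample size and rate of recruitment:** difference 30,000 counts/day; SD 101,600 (read as counts/day, although the sentence ends in minutes); 92 per arm at each factorial margin; 5% significance (taken as two-sided, since the article does not say); stated power 80%.

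**Assumed:** r, the correlation between baseline and one-month counts/day. The article does not give it, so a range is shown.

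**Step 1: the stated figure.** For two unadjusted groups, n per arm = 2 × [(1.960 + 0.842) × 101,600 / 30,000]² ≈ 180.0. This rounds up to 181, and the two-sample t-test also gives about 181. The stated 92 is not reproduced. At 92 per arm the standard error is 101,600 × √(2/92) ≈ 14,980, and 30,000 / 14,980 ≈ 2.00. Power is 51.7% by the normal approximation and 51.3% by the t-test.

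**Step 2: effect of using baseline.** Relative to the unadjusted variance, the factors are:

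- baseline as covariate: 1 − r²
- change with no baseline covariate: 2(1 − r)

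Example at r = 0.5: the adjusted SD is 101,600 × √0.75 ≈ 87,988 and the standard error is 87,988 × √(2/92) ≈ 12,973. The ratio is 30,000 / 12,973 ≈ 2.31, and power is about 63%. Unadjusted change has factor 2 × 0.5 = 1, so power stays at 51%.

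**Step 3: power at 92 per arm (two-sample t-test, two-sided 5%).**

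| r | No use of baseline | Change, no covariate | Baseline as covariate |
|---|---|---|---|
| 0.3 | 51% | 39% | 55% |
| 0.5 | 51% | 51% | 63% |
| 0.6 | 51% | 61% | 70% |
| 0.7 | 51% | 73% | 80% |
| 0.8 | 51% | 88% | 91% |

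**Step 4: what does not depend on the assumed r.** The covariate-adjusted variance divided by the unadjusted-change variance is (1 − r²) / [2(1 − r)] = (1 + r)/2, which is below 1 for any r below 1. The factor 1 − r² is below 1 for any non-zero r. The direction therefore holds throughout the range, and only the size depends on r.

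**Step 5: change with a covariate.** If change is regressed on treatment and baseline, moving baseline to the right-hand side gives follow-up regressed on treatment and baseline, with the baseline slope raised by 1. The treatment effect and its standard error are identical. Any loss for the other outcomes comes from omitting the covariate, not from using change as the response.

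**Limit of the check.** These figures are for means on a linear scale. The stated model is a count GLM reporting rate ratios, so they approximate the gain and are not the power of that model.

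**The case against.** The strongest reply is that this argues from silence. The abstract sentence gives a contrast and a time point, not a model. The Statistical analysis section lists no model terms at all, not even the two treatment factors, so a missing baseline term says little about what was intended. The article condenses a fuller protocol, and a covariate list is commonly left to that or to the statistical analysis plan, neither of which is shown. Requiring a valid baseline week may itself suggest that baseline was meant to be used. Appropriate methods applied to change could include a baseline covariate. The gain may also be small: at r = 0.3, power rises only from about 51% to 55%.

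Much of this stands. A reader might infer that the trial plans an unadjusted primary comparison and raw change scores elsewhere. The document does not support that, because it neither states nor excludes adjustment in either place.

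What the reply does not remove is that the section is specific on other matters (distribution family, effect measure, wear rule, bout definition, imputation). Its account of the primary contrast, the sample size and the other outcomes nowhere gives the baseline value a role as a covariate. The data are collected, required for analysis and free to use, so the plan should say how they enter.

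**Conclusion.** The point holds as one of specification. The primary analysis is described as a one-month difference from a count GLM with no stated baseline term, and the other parameters as change with no stated baseline covariate. Stating the adjustment would improve precision for any non-zero r. On the linear approximation, power at 92 per arm would rise from about 51% to between 55% (r = 0.3) and 91% (r = 0.8).

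Two further readings go too far. First, a reader might infer that baseline adjustment restores the stated 80% power. It does so only if r is about 0.70 or more, which the article does not support with any figure. The failure of 92 per arm to reproduce as a two-group comparison is a separate sample-size problem that adjustment does not excuse. Second, a reader might infer that the count model must give way to linear analysis of covariance. Nothing here requires that, since a GLM can carry the covariate. An unadjusted comparison would still be valid under randomisation, so what is at stake is precision and chance imbalance, not bias.

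**What to change.** - **Primary outcome.** Keep the stated GLM and rate ratio. Specify that the model contains the risk-estimate factor, the lifestyle-advice factor and baseline counts/day (for example, logged) as a covariate.
- **Continuous clinical and biochemical outcomes.** Specify that the baseline value is a covariate, in place of unadjusted change. Either follow-up or change may be the response, since in a linear model the treatment effect is the same.
- **Power statement.** If adjustment is relied on for power, state the assumed baseline-to-follow-up correlation and its source.

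The cost is wording, settled before outcome data are examined by group. No new measurements are needed. For the primary outcome no further participants are lost, because a valid baseline week is already a condition of being analysed.

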**Discussion:**

This is a pilot trial seeking to demonstrate in a real world setting, proof of principal that provision of personalised risk information can contribute to behaviour changes aimed at reducing CVD risk. This study will increase our understanding of the links between the provision of risk information and behaviour change and if successful, could be used in clinical practice with little or no modification.

## Background

Assessment of physical activity is a key element of CVD risk evaluation [1]. A lack of regular physical activity may contribute to the early onset and progression of cardiovascular disease (CVD) in all individuals and almost any increase in physical activity is likely to result in health benefits. Physical activity has a wide variety of beneficial effects on the course of atherosclerosis, resulting in a 20–25% reduction in overall mortality[2].

For individuals with type 2 diabetes CVD risk is an immense problem as they have a 2–4 times greater CVD risk compared with non-diabetic individuals, even after adjustment for age, ethnicity, income, cholesterol level, systolic blood pressure and smoking[3]. Importantly, it is now recognised that increased risk of CVD is apparent long before the diagnosis of type 2 diabetes is made [4-6]. Physical activity reduces CVD risk and its impact is greatest in those at highest risk[7]. This is seen even when adjusting for weight loss indicating that physical activity is an independent risk factor for CVD and can provide some protection in those at highest risk[7,8]. In a meta-analysis of trials to promote physical activity among people with type 2 diabetes a 0.6% reduction in HbA1c was seen[9].

Individuals at risk of developing type 2 diabetes also benefit from physical activity as lifestyle interventions including physical activity have been shown to prevent or delay the onset of type 2 diabetes [10-12].

The beneficial effects of physical activity on CVD risk are mediated through a lowering of blood pressure, increasing HDL cholesterol, reducing body fat and reducing insulin resistance[7]. To date trials evaluating behaviour change interventions have been limited by a lack of use of objective measures of physical activity favouring imprecise self-report methods[13].

The study, conducted in individuals at high estimated CVD risk, aims to determine if the provision of individualised information about future CVD risk can be used successfully to change behaviour. Research from other fields indicates that interventions including an individualised risk estimate can have an impact on behaviour[14], particularly in those whose risk is higher than average for their age and sex[15].

Brief lifestyle interventions have been shown to be effective in preventing and treating type 2 diabetes[16] and in preventing the complications of diabetes including reducing CVD risk[17,18]. We expect to find that providing personalised CVD risk information or lifestyle advice to individuals at increased risk of CVD can increase the amount of physical activity they perform per day, compared with risk factor information alone or no lifestyle information. In turn, we expect also to see improvement in the levels of the other CVD risk factors measured.

## Methods/Design

### Primary objective

To determine the efficacy of each intervention for increasing physical activity at one month compared with CVD risk factor values and to determine if brief lifestyle advice versus no lifestyle advice can increase physical activity at one month.

### Secondary Objectives

To determine the efficacy of each intervention in modifying the following CVD risk factors: smoking status, fruit and vegetable intake, alcohol consumption, fasting and 2-hour post-challenge plasma glucose, fructosamine, waist circumference, weight, BMI, total cholesterol, HDL cholesterol, LDL cholesterol and triglycerides, systolic and diastolic blood pressure, estimated 10-year CVD risk, estimated risk of diabetes and body fat percentage.

### Tertiary Objectives

To determine the efficacy of each intervention on anxiety, quality of life, self-regulation, worry about future risk of heart attacks, intention to increase physical activity and recall of risk information given.

## Methods/design

### Study Design

This is a pilot study to investigate the feasibility of a larger scale randomised controlled trial and is a 2 × 2 factorial design with 46 participants in each cell (Figure 1). This is considered to be the most appropriate and efficient method of answering the research question posed. Each participant will receive an individualised cardiovascular disease risk estimate or CVD risk factor values plus standardised brief lifestyle advice or not. The trial is being managed by a UK Clinical Research Collaboration Clinical Trials Unit, the Diabetes Trials Unit, University of Oxford, UK. Ethical approval was granted by the Milton Keynes Local Research Ethics Committee in September 2007.

**Figure 1 F1:**
[figure not shown]

Physical activity, clinical and psychological information will be collected before randomisation and one month after delivery of the intervention. A personalised CVD risk estimate and lifestyle advice will be provided to all participants at the end of 4 weeks making it a waiting-list control design. The inclusion of a control group receiving neither a risk estimate or lifestyle advice but undergoing baseline and follow up measurement will control for Hawthorne effects[19].

### Practices and participants

GP practices from Oxfordshire have been recruited. Participant eligibility criteria are adults aged 40–70 years, estimated 10-year CVD risk ≥20%, not known to have cardiovascular disease as defined by a history of myocardial infarction, other incident ischaemic heart disease, stroke, coronary or peripheral revascularisation, or transient ischaemic attack, not known to have a physical disability or other condition reducing the ability to walk, and able to read and write English.

### Screening eligibility

Participating practices allowed a member of the research team who holds an honorary contract with the Primary Care Trust, to identify eligible participants from practice databases. Once identified, lists of potentially eligible participants were constructed and general practitioners asked to review the list for suitability prior to sending out invitations to take part in the study. Participant invitation letters were sent out randomly in batches of 60 (figure 1).

### Telephone contact

Once a participant has expressed interest in taking part in the study by returning a reply slip in a prepaid envelope or by emailing or telephoning the research team a researcher obtains verbal consent and arranges a date and time for visit 1. ActiGraph accelerometers (model GT1M, Manufacturing Technology, Fort Walton Beach, FL) are then mailed to recruited participants approximately one week prior to visit 1 in order to reduce the number of visits and to reduce the potential effect of measurement on baseline physical activity. Simple instructions on how to use the device are provided and participants are asked to wear the accelerometer for seven days in total over a mixture of week and weekend days. Accelerometers are worn on an elastic belt around the waist and are removed for sleep, bathing, showering and swimming.

### Baseline assessment

Baseline clinical assessment is conducted by a clinical researcher and research nurses prior to randomisation in a clinical research unit. Written informed consent is collected at this visit. Medical history, demographic details, age at leaving school and electoral ward are collected. A 75 mg anhydrous oral glucose tolerance test (0 and 120 minute glucose sampling) is conducted and fasting blood samples taken for total, LDL and HDL cholesterol, triglycerides, HbA1c, serum cotinine, plasma vitamin C and fructosamine assessment. Anthropometric measurements are taken (resting blood pressure, height, weight, waist circumference, body fat percentage). Smoking status, current medication and self-reported alcohol intake is recorded. An ECG is performed. A booklet of questionnaires comprising the short-form Spielberger anxiety inventory[20], EQ5D questionnaire[21], Illness perception questionnaire, adapted Lerman cancer worry scale[22], psychological impact questionnaire, Recent Physical Activity Questionnaire (RPAQ) and A Fear-Avoidance Beliefs Questionnaire (FAB) is completed by each participant. Once these data have been collected the participant is randomised and any interventions delivered at this study visit.

### Outcome assessment

Follow-up at four weeks occurs for all measures including oral glucose tolerance test, blood samples, anthropometric measurements, smoking status, current medication, alcohol intake and questionnaires with the addition of a recall of risk information questionnaire. Physical activity is again measured by accelerometer for seven days in the week before the second study visit.

### Randomisation

Computer randomisation is used to allocate participants to each of the interventions in blocks of four. No minimisation is used. Research nurses who input data are blind to intervention allocation. One research fellow will remain unblinded in order to deliver the interventions. All research nurses working on the study have undergone training in the protocol and electronic data capture system prior to the study commencing.

### The interventions

Participants randomised to receive a risk estimate will have their 10-year CVD and fatal CVD risk estimated using a modified version of the UKPDS Risk Engine[23]. This has an interface designed specifically for use in the study with the aim of achieving maximum comprehension by participants. Participants will be shown their current risk and also their 'achievable risk' i.e. the risk estimate they could achieve if they were to meet current targets[24] for systolic blood pressure, LDL cholesterol, HbA1c and smoking cessation (if applicable). Participants will be given a UKPDS Risk Engine print out showing their current and achievable risk. Those participants not randomised to a 10-year CVD risk estimate will be informed of their LDL cholesterol, fasting plasma glucose and blood pressure values and informed if they are elevated according to current guidelines[24].

The lifestyle intervention used is based on self-regulation theory [25] and involves goal setting and steering behaviour towards goal achievement[26]. It also acknowledges the other priorities in participant's lives including family and financial constraints and encourages them to set goals around these commitments and states that any change in a positive direction is beneficial. This theoretical approach has been used in other studies attempting to motivate behaviour change in a similar population [27]. Participants randomised to receive the lifestyle advice intervention will receive a computer presentation. This presentation will focus on encouraging participants to increase their physical activity and fruit and vegetable intake and to decrease their alcohol intake and stop smoking if necessary. The physical activity goal will be 30 minutes of brisk walking per day in line with current guidelines[28]. Instant feedback of physical activity for example by using pedometers, is not provided as part of the study. The fruit and vegetable goal will be five portions per day in line with current UK government recommendations [29]. A reduction in alcohol consumption will only be advised if current intake is above UK government recommendations (not more than 3–4 units per day for men and 2–3 units per day for women)[30].

